**Methods and design:**

Individuals (18−30 years) will participate in same-sex pairs in two experiments. In the first experiment (triadic interaction), both participants attentively watch unpleasant, neutral and pleasant pictures, and read/listen to standardized scripts (unpleasant, neutral, and pleasant, respectively) for the imagination task. In the second experiment, participants will read out three scripts (unpleasant, neutral, pleasant) to each other, followed by a joint imagination period. Stimuli will be presented in counterbalanced orders. After each picture and imagination, participants rate their subjective arousal and valence. In the beginning and in the end of the procedure, dyads rate their relationship, sympathy, and bonds (Working Alliance Inventory subscale). Heart rate, electrodermal activity and electroencephalogram will be continuously measured during both experiments using portable devices (EcgMove4 and EdaMove4, nine-channel B-Alert X-Series mobile-wireless EEG). Synchrony analyses will include the dual electroencephalography analysis pipeline, correlational analyses and Actor–Partner Interdependence Models.

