### 2.3. Procedure

After arrival to the lab, participants will provide written informed consent to the study protocol approved by the ethics committee of the University Medicine Greifswald and sensors will be attached according the manufacturers’ manuals. If necessary, participants will get to know each other introducing themselves briefly (first name, age). Then, they will fill in the modified Working Alliance Inventory [WAI-SR, German; (45)] bonds-subscale (Items 3, 5, 7, 9, see Supplementary material 2) and rate their relationship and sympathy on a nine-point Likert scale (1 = “completely unknown/do not like at all” to 9 = “very well-known/like very much”; ratings are never revealed to the partner and participants have to sign a declaration of confidentiality). Data acquisition will take place in a sound-attenuated, dimly lit cabin. Following a 10 min baseline (rest, black screen), experiments A and B will be conducted in counterbalanced order. Finally, individuals will fill in the bonds-subscale (WAI-SR) and will be told the objectives of the experiment. Apart from the experimental interaction procedure, participants will be instructed neither to engage in conversation, nor to communicate *via* gesture or mimics.

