Moreover, correlational analyses and Actor–Partner Interdependence Models (APIM) are planned to analyze the influence of synchrony on subjective and interpersonal ratings (51, 52). Separate APIMs are planned for each measure (Heart rate, skin conductance, EEG) in the different tasks (independent variables) and subjective bonds-rating after the experiments (dependent variables).

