In line, the secondary outcomes include the relationship between physiological and neural synchrony and (1) subjective emotional experience, and (2) interpersonal relationship. Whilst it is very likely that high physiological and neural synchrony will go along with similar subjective ratings, at least on the arousal dimension (30, 53), there is some evidence for more positive relationships with higher synchrony (17, 20, 61); but this correlation has been mainly observed in parent-child and romantic partner interactions, and has been shown to grow with experience [(18); for review, see Koole et al. (7)]. Therefore, this relationship might be more pronounced in individuals who indicate being more familiar with each other in the beginning of the experiment. Notably, higher SCL synchrony has been associated with therapeutic bond during imagery, but not during application of cognitive-behavioral strategies (such as psychoeducation or identification of automatic conditions) suggesting that the association between synchrony and (therapeutic) relationship might also be task-dependent (61).

Fundamental understanding of interpersonal synchrony is critical to further examine interactions in the psychotherapy setting, and to potentially positively influence the therapeutic relationship through targeted interventions in a next step (e.g., neurofeedback, biofeedback). This approach is in line with the vision of translating basic bio-psychological research into disorder-independent clinical psychotherapy research—and back (3). Here, we focus on (neuro-) physiological correlates of emotion processing, which would mainly relate to the function domain of negative emotionality in mental disorders. Thus, research using and extending the present approach might identify dysfunctional (emotional) interaction patterns in sub-clinical and clinical samples from a *trans*-diagnostic perspective. Only recently, Saul et al. (62) proposed to not only investigate inter-brain synchrony in social anxiety disorder, but also to improve treatment *via* adding neurofeedback, pointing to fascinating new research perspectives. Moreover, as Koole and Tschacher (7) point out, the In-Sync model of psychotherapy provides the framework for training psychotherapists using feedback on movement and language synchrony in order to improve the therapeutic relationship. This might also include physiological and neural feedback strategies.

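### The task-by-task APIMs share one end-of-session bonds rating, with no stated use of the starting rating or of experiment order, so they show associations but cannot credit bond to Experiment A or B

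*Protocol article*

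**What the plan says.** All places are in the protocol article.

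- **Models (Section 2.5).** "Separate APIMs are planned for each measure (Heart rate, skin conductance, EEG) in the different tasks (independent variables) and subjective bonds-rating after the experiments". The bonds rating is the dependent variable in every one of these models.
- **Order (Section 2.3).** "Following a 10 min baseline (rest, black screen), experiments A and B will be conducted in counterbalanced order".
- **Rating at the start (Section 2.3).** "Then, they will fill in the modified Working Alliance Inventory [WAI-SR, German; (45)] bonds-subscale", together with ratings of relationship and sympathy.
- **Rating at the end (Section 2.3).** "Finally, individuals will fill in the bonds-subscale (WAI-SR) and will be told the objectives of the experiment". No rating between the experiments is described.
- **Abstract (Methods and design).** "In the beginning and in the end of the procedure, dyads rate their relationship, sympathy, and bonds". By this account all three ratings are repeated at the end.
- **Hypothesis (Section 2.6.3).** Pairs with higher synchrony during the picture and imagination tasks are expected to give better bonds ratings afterwards. No contrast between the triadic and the dyadic experiment is stated.
- **Discussion (Section 3).** The link may be stronger in pairs who know each other better at the outset. Commenting on a cited study, the article adds that "the association between synchrony and (therapeutic) relationship might also be task-dependent".

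**The concern.** The models are specified task by task, but their outcome is not task-specific. Every pair completes both experiments before the only post-experiment rating, so one number per person serves as the outcome for all tasks. Two consequences follow.

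1. **Attribution.** If pairs who synchronise in one experiment also tend to synchronise in the other, a model holding only one experiment's synchrony picks up the other's association with bond.
2. **Starting rapport.** Partners may already know each other. Rapport brought into the laboratory can raise both synchrony and the end rating. In the second experiment, rapport gained in the first can do the same. Sections 2.6 and 2.6.3 speak of the influence of synchrony on ratings, and an unadjusted association with the end rating does not carry that meaning.

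At stake is how the interpersonal part of the secondary outcome may be worded. Separately, the Abstract and Section 2.3 give different lists of end ratings. If study staff follow Section 2.3, end ratings of relationship and sympathy will not exist.

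**Working it through.** **1. The plan's own figure.** Section 2.5 gives N = 42 for the emotion-by-partner ANOVA (alpha 0.05, power 0.95, partial eta squared 0.06).
- f² = 0.06 / 0.94 = 0.0638, so f = 0.2526.
- Assumed, because not stated: correlation among measures 0.5, sphericity epsilon 1. There are 3 measurements and 2 groups.
- Noncentrality = f² × N × 3 / (1 − 0.5) = 0.0638 × 42 × 3 / 0.5 ≈ 16.1, with df 2 and (42 − 2) × 2 = 80.
- Power = 0.9506, so N = 42 is reproduced. It sizes the emotion effect and was not derived for the synchrony-bond models.
- If N counts individuals, there are 42 / 2 = 21 pairs, or 10 and 11 per experiment order.

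**2. Timeline for one pair.** Start ratings, baseline rest, first experiment, second experiment, bonds rating. Change in bond over the whole session can be calculated. Change over one experiment cannot. Counterbalancing evens out which experiment comes last across pairs, but it does not divide one rating between two experiments within a pair.

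**3. Attribution, illustrated.** Let standardised synchrony in A and B correlate r across pairs, and let end bond depend on B only, with slope b. The separate model for A then has expected slope b × r. With b = 0.5 this is 0, 0.15, 0.25 and 0.35 for r = 0, 0.3, 0.5 and 0.7. Simulation used 21 pairs, 4,000 runs per row, pair-level regression and a two-sided 5% test:

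| r | Separate model: A significant | Joint model: A significant | Joint model: B significant |
|---|---|---|---|
| 0 | 4.6% | 4.9% | 65% |
| 0.3 | 10.1% | 5.0% | 59% |
| 0.5 | 18.8% | 4.8% | 54% |
| 0.7 | 34.7% | 4.7% | 39% |

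Both b and r are assumptions; the article gives neither. The simulation is a simplified regression, not a full APIM, and contains no order effect and no starting rapport. It shows only that separate models lend one experiment the other's association when r is above zero, and that a joint model removes this at a cost in power.

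**4. Starting rapport.** If starting rapport correlates a with synchrony and c with end bond, and synchrony itself does nothing, synchrony and end bond still correlate a × c. Adjusting for the starting rating removes this to the extent that the rating captures rapport. The documents give no values for a or c, so no size is claimed.

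**5. The two lists of ratings.**

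| Source | Start | End |
|---|---|---|
| Abstract | relationship, sympathy, bonds | relationship, sympathy, bonds |
| Section 2.3 | relationship, sympathy, bonds | bonds only |

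Sections 2.5, 2.6 and 2.6.3 name only the bonds or WAI-SR rating as the interpersonal outcome after the experiments.

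**The case against.** The strongest reply is that the plan never promises attribution. Section 2.6.3 expects an association between synchrony and end bond, and that is what the models estimate. This stands, and it confines the point to interpretation and adjustment.

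A second reply is that covariates in a secondary model are usually left to a full protocol or analysis plan, which is not shown. That also stands in part: the silence on order and starting bond is not an error in itself. What the article does fix is the rating times and the separate models sharing one outcome, and those are what limit the inference.

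A reader might go further in four ways that the documents do not support:

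- **That a stated triadic-versus-dyadic aim fails.** The Discussion remark on task dependence interprets a cited study that compared imagery with cognitive-behavioural strategies. It is not an aim of this study.
- **That the order of experiments creates an imbalance or a recency bias.** On the Section 2.5 durations, Experiment A takes about 3 × 15 + 2 × 3.5 = 52 min and Experiment B about 2 × 3.5 = 7 min, so the gap between the face-to-face task and the rating differs by order. That is elapsed time; nothing in the article shows that it shifts a bonds rating. Having 10 and 11 pairs per order is balance.
- **That a rating between the experiments is required.** It could prime rapport and alter synchrony in the second experiment. It also would not separate picture viewing, silent reading and listening, which all sit inside Experiment A. A single end rating is a defensible choice for a pilot.
- **That a planned analysis loses its data if sympathy is not rated at the end.** No stated analysis uses end sympathy.

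**Conclusion.** The point holds as a limit on one secondary outcome. The separate models can estimate each task's association with final bond. They cannot credit bond to Experiment A or Experiment B, and without the starting rating they cannot set aside rapport that was there from the beginning. The size is not knowable from the article. Under the assumed slope of 0.5, false credit to the other experiment occurs in 10% to 35% of studies for cross-experiment correlations of 0.3 to 0.7, and stays near the nominal 5% if that correlation is zero. The primary emotion analysis and N = 42 are untouched.

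The conflict between the Abstract and Section 2.3 over the end ratings is real and rests on no assumption. Its consequence is uncertainty about what will be collected.

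**What to change.** 1. In the end-bond models, adjust for each partner's starting bonds rating and for order (A first or B first). Both are already available. The cost is a few degrees of freedom: at pair level with 21 pairs, adding the pair's mean starting rating and order to the synchrony term leaves 21 − 4 = 17 residual degrees of freedom in place of 21 − 2 = 19.
2. Add a sensitivity model with Experiment A and Experiment B synchrony together. State that precision is low at about 21 pairs; in the illustration, power for the true effect falls from 65% to 39% as the correlation rises from 0 to 0.7.
3. Describe per-task results as associations with end-of-session bond, and do not speak of the influence of one task.
4. Optional, only if attribution to A or B is wanted: repeat the four bonds items between the experiments. This costs about one minute per participant and carries a risk of priming the second experiment.
5. Reconcile the Abstract with Section 2.3. Either collect relationship, sympathy and bonds at the end, or correct the Abstract to bonds only. If the ratings are to be collected, this must be settled before data collection, since a rating not taken cannot be recovered.

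### The bond models use only the post-experiment rating and give no stated role to the baseline bond, relationship and sympathy ratings already collected, so prior acquaintance may account for part or all of any synchrony–bond association

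*Protocol article*

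**What the plan says.** **Model.** Section 2.5 of the protocol article names both sides of the bond models. For the predictors: "Separate APIMs are planned for each measure (Heart rate, skin conductance, EEG) in the different tasks (independent variables". For the outcome: the "subjective bonds-rating after the experiments (dependent variables". Sections 2.6 and 2.6.3 again take the rating after the experiment as the outcome. Section 2.5, section 2.6 and the title of section 2.6.3 all speak of an influence of synchrony on ratings.

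**Baseline data.** Section 2.3 collects the same subscale before the experiments: "Then, they will fill in the modified Working Alliance Inventory [WAI-SR, German; (45)] bonds-subscale". Participants also "rate their relationship and sympathy on a nine-point Likert scale" at that point. No analysis text gives these ratings a role as covariate, change score or moderator. The only covariates mentioned anywhere are the emotion-regulation scores, in the Discussion.

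**Acquaintance.** Section 2.1 sets no rule on whether partners know each other, and section 2.3 allows for both cases: "If necessary, participants will get to know each other introducing themselves briefly". On the link between synchrony and relationship, the Discussion expects that "this relationship might be more pronounced in individuals who indicate being more familiar with each other in the beginning of the experiment".

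**End-of-session ratings.** The abstract says: "In the beginning and in the end of the procedure, dyads rate their relationship, sympathy, and bonds". Section 2.3 lists only the subscale at the end: "Finally, individuals will fill in the bonds-subscale (WAI-SR) and will be told the objectives of the experiment".

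**The concern.** A pair who arrive as friends probably start with a higher bond and carry it into the second rating, which uses the same subscale in the same session. The Introduction and section 2.6.3 cite evidence that more positive relationships go with higher synchrony. If that holds here, friends would score higher on both sides of the model even if synchrony during the tasks changed nothing. A model of the post-experiment rating alone cannot separate that pattern from an effect of synchrony, yet the article words its result as an influence.

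There is also a loss of precision. The sample size was set for the emotion ANOVA, not for the bond models. Differences in bond that existed before the session stay in the residual, although a measurement that could remove much of them is already available.

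**Working it through.** **Inputs from the article.** Total N = 42, partner as a two-level factor, alpha 0.05, power 0.95, partial η² = 0.06 (section 2.5). Hence 42 / 2 = 21 dyads.

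**Inputs assumed, because the documents give none.** a = correlation of baseline bond with synchrony, 0.3–0.4. r = correlation of baseline with post-experiment bond, 0.6–0.8. Wider ranges (a = 0 to 0.5, r = 0.5 to 0.8) were used in a simulation. All calculations use one bond score per dyad, which simplifies the planned models.

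**1. The article's own figure.** f² = 0.06 / 0.94 = 0.0638. With three conditions, two groups, and an assumed correlation of 0.5 and sphericity, λ = 0.0638 × 42 × 3 / 0.5 ≈ 16.1 on 2 and 80 degrees of freedom. Power is 0.951, and 42 is the smallest even N that reaches 0.95. The figure reproduces and is not affected by this point. It says nothing about the bond models.

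**2. Spurious correlation with no direct effect of synchrony.** The correlation of synchrony with post-experiment bond is then a × r.
- Low end: 0.3 × 0.6 = 0.18
- High end: 0.4 × 0.8 = 0.32
- If a = 0: 0, whatever r is

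**3. Consequence for a two-sided 5% test with 21 dyads.** By Fisher's z, the test statistic is centred at atanh(a × r) × √(21 − 3).
- 0.18: 0.182 × 4.243 = 0.77, rejection rate about 12%
- 0.32: 0.332 × 4.243 = 1.41, rejection rate about 29%

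In the simulation, a = 0.2 to 0.5 with r = 0.5 to 0.8 gave about 7% to 45% unadjusted and about 5% adjusted. With a = 0, both analyses stayed at about 5%.

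**4. Precision.** With no direct effect, the residual variance is 1 − a²r² unadjusted and 1 − r² adjusted. The synchrony variance left after adjustment is 1 − a². The standard-error ratio, adjusted to unadjusted, is therefore √[(1 − r²) / ((1 − a²)(1 − a²r²))].

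| r | a = 0 | a = 0.3 | a = 0.4 |
|---|---|---|---|
| 0.6 | √0.64 = 0.80 | √(0.64 / (0.91 × 0.9676)) = 0.85 | √(0.64 / (0.84 × 0.9424)) = 0.90 |
| 0.8 | √0.36 = 0.60 | √(0.36 / (0.91 × 0.9424)) = 0.65 | √(0.36 / (0.84 × 0.8976)) = 0.69 |

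The standard error falls by 10–15% at r = 0.6 and by 31–35% at r = 0.8. Reductions of 20–40% apply only in the column a = 0, where there is no bias to remove.

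**5. Power without confounding.** For a standardised synchrony effect of 0.4, 21 dyads and a = 0, simulated power is about 45% unadjusted. Adjusted, it is 56%, 76% or 92% for r = 0.5, 0.7 or 0.8. If baseline bond were useless (r = 0), adjustment would lower power from about 45% to about 42%.

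**The case against.** **Silence is not exclusion.** Section 2.5 is a short summary in a journal article, and covariates are often left to a fuller plan. A reader might infer that the baseline ratings will go unused or that adjustment has been ruled out. The documents do not support that; they only state no use for these ratings. The point still stands, because the article does name predictors and outcome and repeats the post-only outcome in two further sections.

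**Confounding is not demonstrated.** A reader might infer that friendship alone does produce the predicted association. That needs baseline bond to correlate with synchrony in this setting, and no figure is given. The Discussion passage on familiarity describes moderation (a stronger link in familiar pairs), not that familiar pairs synchronise more. General support comes only from the Introduction and section 2.6.3. The number of acquainted pairs is also unknown. This objection stands and limits the claim to an expected risk.

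**Bias and precision trade off.** A reader might combine the 0.18–0.32 bias with a 20–40% precision gain. Step 4 shows that both cannot hold together.

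**Small sample, secondary outcome.** Baseline bond, familiarity and an interaction are three terms, probably collinear, in models with 21 dyads. That argues for a small fix, not for leaving baseline out. The primary question is untouched, and the abstract itself speaks of an association.

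**Conclusion.** The point holds as a recommended change to a secondary analysis. As written, the bond models cannot separate synchrony during the tasks from the relationship the pair brought with them, and so do not support the word influence. Under the assumed correlations, the spurious correlation is 0.18–0.32 and the standard error of the synchrony coefficient falls by about 10–35% with adjustment. If synchrony is unrelated to baseline bond there is no bias, and the only loss is precision (20–40% for r = 0.6–0.8). Every one of these sizes rests on assumed correlations and one bond score per dyad. Only the omission itself is read from the text.

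The disagreement over end-of-session ratings is real but separate. It adds nothing to the case for adjustment.

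**What to change.** - State that every bond model includes the baseline bonds score as a covariate, and that this is the pre-specified analysis. It costs one degree of freedom, or two if the partner's baseline score is also entered. No new instrument is needed.
- Keep the baseline relationship (familiarity) rating and its interaction with synchrony as exploratory or sensitivity terms, given 21 dyads.
- Report the result as an association given baseline bond. A four-item baseline is measured with error, so adjustment reduces confounding but may not remove it.
- Separately, reconcile the abstract with section 2.3 on which ratings are repeated at the end. If the abstract is right, this adds two short items to the end of the session; if section 2.3 is right, only the abstract needs correcting.

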### 2.6. Outcome and hypotheses

Primary research question is the successful implementation of the picture viewing and imagination paradigms from an individual setting into the two-person interaction, aiming at the replication of the enhanced attention to emotion effect [motivated attention; (30)] in subjective ratings (SAM), physiological (ECG, EDA) and neuronal (EEG) markers, and the development and testing of new data analysis strategies. Secondary outcome will be the influence of synchrony in physiological and neuronal activity during picture viewing and imagination on subjective emotion experience and interpersonal ratings after the experiment (WAI-SR).

#### 2.6.1. Emotion effect

In line with standard ratings and previous studies, we expect higher subjective arousal ratings for emotional, relative to neutral, pictures and scenes, and valence ratings unpleasant < < *cps*:*it* > *neutral* < /*cps*:*it* > < pleasant according to the biphasic model (30). During picture viewing, we expect emotionally arousing pictures to evoke more pronounced initial HR deceleration, whereas pleasant pictures will provoke higher post-orienting acceleration relative to unpleasant stimuli over time (30). Higher skin conductance levels are expected for emotionally arousing, relative to neutral pictures (30). In ERPs, emotional modulation of the EPN is expected between 150 and 350 ms post-stimulus onset (36). Over centro-parietal electrodes, elevated Late Positive Potentials (LPPs) for emotionally arousing, relative to neutral pictures, are expected, starting at about 400 ms post-stimulus onset (23, 24, 35).

During imagery, analogous reaction patterns are expected for heart rate and skin conductance [(29, 37, 38); for summary, see Ji et al. (39)]. Possibly, the LPP emotion effect might emerge over more posterior electrodes, compared to picture viewing (40), if it is not blunted at all during imagery (41).

